### Intervention

These eligible participants will ingest 2 g granules of JTW or placebo, twice a day at 1600 hours and 2100 hours for 1 week and present themselves at the termination of medication, followed by a scheduled examination.

Both JTW and placebo are manufactured by the Kangren Pharmaceutical Factory according to good manufacturing practice standards. JTW will be produced in the form of granules with a yellowish-brown color. The medication will be 2 g, containing 1.1 g JTW soft extract with 0.37 g of lactose hydrate and 0.88 g of corn starch as the excipient. The JTW soft extract will be made of a water extract of a mixture of two herbal medicines, as follows: Rhizome Coptidis (10 g) and Cortex Cinnamomi (1 g). The placebo will consist of corn starch, lactose hydrate, citric acid, and caramel color. The placebo and JTW will have the same appearance and color.

### Medication compliance monitoring

To ensure compliance with the medication, participants will be asked to count the actual intake and return the empty wrapping papers for the medication and any remaining medicine.

### Prohibition and permission for concomitant treatment

The use of any sedative hypnotics to help sleep will be prohibited during the study.The use of any traditional medicine designed to treat insomnia, except for the intervention of this trial, will be prohibited during the study.The use of functional foods or other medications intended to improve the symptoms of insomnia will be prohibited during the study.Any psychotherapy for accelerating sleep quality will be prohibited during the study.Medications used to treat other chronic diseases at the beginning of this trial will be allowed.Routine physical training before the start of this clinical trial will be allowed.Any change in medications or physical exercise during the study will be recorded in a clinical report form.

### Outcome measurement

#### Primary outcome

We chose 1 week to assess the curative effect of JTW based on: (1) our previous experimental results and findings on animal sedation and hypnosis [16]; and (2) our clinical experience with patients using JTW.

##### Pittsburgh Sleep Quality Index

The PSQI will be used at the baseline and the end of the drug intervention. The PSQI version used in this study is a 19-item self-reported retrospective questionnaire to access the quality of sleep in the past 7 days, and it is designed to measure seven domains called component scores: subjective sleep quality; sleep latency; sleep duration; habitual sleep efficiency; sleep disturbances; use of sleep medications; and daytime dysfunction [16, 17]. Component scores range from 0 (no difficulty) to 3 points (severe difficulty), and when summed, produce a global score in the range of 0–21. A higher score denotes worse sleep. These syndromes are categorized as mild (0–1), moderate (2–7), or severe (≥ 8) [18]. Then, the scores the participants obtained at baseline will be recorded as score 0, and the scores obtained at the end of drug intervention will be recorded as score 1. The recorder will calculate the reduction rate (RR) according to the following formula: RR = (score 1–score 0)/score 0*100%. Finally, we will assess the clinical curative effect of every participant based on the results of the RR. RR values > 75% will be regarded as a clinical cure, RR values between 50%–75% will be considered as a clinical effective, RR values between 25%–50% will be recognized as a clinical success, and RR values < 25% will be considered ineffective. The primary outcome is defined to have a value of 0 if RR is < 25% (ineffective) and 1 if RR is > 25% (clinical cure, clinically effective, or clinical success). The proportion of 1s (i.e. RR ≥ 25%) will be compared between the treatment and placebo groups.

In addition, Liu et al. [18] presented their opinion that the PSQI is suitable for Chinese patients after they conducted reliability and validity tests [19].

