### Statistical analysis

We will use two-sided *p* values for the primary outcome and for all secondary outcomes and safety variables. For the primary outcome, we will use Fisher’s exact test to test the hypothesis at null: the treatment has the same efficacy as the placebo. For each secondary outcome, defined as the value difference between baseline and end-of-intervention, we will use the following tests: (1) t-test for the continuous PSG variables; Chi-square test for the categorical PSG variables; (2) t-test for the blood-level adenosine and melatonin; (3) t-test for the GABA/Cr ratio; and (4) Wilcoxon rank sum test for the Disharmony Score of Heart and Kidney. For safety evaluation of JTW, a two-sided t-test will be applied to each safety measurement after data normalization.

We define the analysis population as the enrolled participants who have successfully completed the trial. We will characterize the types of individuals who have missing data to better understand the nature the missing mechanisms. We will use statistical models to impute missing values if the assumption of missing at random is met. This can preserve and utilize the information of the non-missing values.

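### The printed reduction-rate formula has its sign reversed: every improvement in PSQI is coded ineffective, and only a worsening of about 25% or more counts as a success

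*Protocol article*

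**What the plan says.** All the elements are in the Pittsburgh Sleep Quality Index section of the protocol article.

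- **Scale:** the seven components "produce a global score in the range of 0–21", and "A higher score denotes worse sleep".
- **Time points:** score 0 is the PSQI at baseline. For the second assessment, "the scores obtained at the end of drug intervention will be recorded as score 1".
- **Formula:** RR, named a reduction rate, is calculated by the recorder "according to the following formula: RR = (score 1–score 0)/score 0*100"%.
- **Categories:** "RR values > 75% will be regarded as a clinical cure"; 50–75% is effective, 25–50% is a success, and below 25% is ineffective.
- **Binary endpoint:** 1 if RR exceeds 25%, 0 if it is below 25%. The sentence on the comparison then describes the successes as RR ≥ 25%.

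The Statistical analysis section applies Fisher's exact test, two-sided, to the primary outcome under the null hypothesis that "the treatment has the same efficacy as the placebo". The Sample size section assumes success rates of 70% on JTW and 40% on placebo.

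**The concern.** On a scale where lower is better, end score minus baseline is negative for anyone who improves. The cut-offs are all positive, so the formula and the cut-offs point in opposite directions. Taken literally, the endpoint measures deterioration and calls it success. An effective JTW would then show fewer successes than placebo, or no difference.

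Three features of the design make this more than cosmetic:

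- A recorder applies the formula to each participant, so wrong values could be stored before any statistician sees them.
- The primary test is two-sided, so it would not itself flag a result in the wrong direction.
- The statisticians are blinded to allocation, so a difference between arms A and B would not look wrong until the codes are opened.

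**Working it through.** **Inputs**

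- PSQI range 0–21, higher is worse; score 0 is baseline, score 1 is end of treatment; the RR formula and the 25% cut (Pittsburgh Sleep Quality Index section).
- Baseline PSQI at least 7 (Inclusion criteria).
- Success rates 70% and 40%, two-sided α of 5%, power 80%, drop-out 20% (Sample size section).

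**1. The plan's own figure.** The article needs 49 per group before drop-out. The usual two-proportion formula gives

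[1.96·√(2 × 0.55 × 0.45) + 0.8416·√(0.7 × 0.3 + 0.4 × 0.6)]² / 0.3² = (1.379 + 0.565)² / 0.09 ≈ 42.

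With the continuity correction this becomes (42/4)·[1 + √(1 + 4/(42 × 0.3))]² ≈ 48.4, so 49. Then 49/0.8 = 61.25, rounded up to 62 per group and 124 in total. The figure is reproduced. It uses only the two assumed rates and does not depend on the sign of RR.

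**2. Single participants.** Printed: RR = (score 1 − score 0)/score 0 × 100%. Reversed: RR = (score 0 − score 1)/score 0 × 100%.

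| Baseline → end | Printed RR | Coded as | Reversed RR | Coded as |
|---|---|---|---|---|
| 12 → 6 | −50% | ineffective | +50% | success (1) |
| 12 → 0 | −100% | ineffective | +100% | clinical cure |
| 12 → 16 | +33.3% | success (1) | −33.3% | ineffective |
| 8 → 15 | +87.5% | clinical cure | −87.5% | ineffective |

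**3. All possible participants.** Fifteen baseline values (7–21) times 22 end values (0–21) give 330 pairs.

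- Improvements: 7 + 8 + … + 21 = 210 pairs. The printed RR is negative in every one, so none is a success.
- Printed RR ≥ 25%: for baselines 7 to 16 the counts are 13 + 12 + 10 + 9 + 8 + 7 + 5 + 4 + 3 + 2 = 73. All are worsenings. With a strict > 25%, the pairs 8 → 10, 12 → 15 and 16 → 20 drop out, leaving 70.
- The largest attainable printed RR is (21 − b)/b for baseline b. At b = 16 it is 31.2%; at b = 17 it is 23.5%. From a baseline of 17 upwards, success cannot occur at all.

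**4. Illustrative size.** The article gives no baseline or change distribution, so these are assumptions: baseline mean 11–14, SD 3, limited to 7–21; SD of change 2.5–4; mean change in each arm set so that the true rates of a 25% reduction are 70% on JTW and 40% on placebo. The printed formula then labels about 0.1–3% of JTW and 1–14% of placebo participants a success. At baseline mean 12 and change SD 3 the figures are about 0.8% and 5%. The direction is reversed throughout.

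**5. Correction elsewhere.** No other section takes an absolute value or reverses the sign. The Abstract speaks only of a mean change in PSQI, and the Abbreviations list only expands RR as a reducing rate.

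**The case against.** The strongest reply is that this is a misprint nobody would follow. RR is called a reduction rate, values above 75% are called a cure, and the sample size section speaks of treatment success. A reader who saw a rise from 8 to 15 classed as a cure would stop and correct the sign. A human recorder applies the formula, so the slip would probably surface on first use. The Abstract, moreover, names the mean change in PSQI as the primary outcome, and a mean change does not pass through this formula.

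Much of this stands. The intended direction is evident, a reversed trial result is not the likely outcome, and the 70% and 40% rates were plainly meant as improvement rates. The simulated rates rest on assumed distributions and do not forecast this trial. The article also does not say where RR values are stored or whether any have been calculated.

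It does not remove the defect. The article gives an explicit formula, not an omission that a fuller document could fill, and that formula contradicts the scale and the cut-offs around it. The Abstract's mean change does not rescue it either: the Statistical analysis section tests the primary outcome with Fisher's exact test, which fits the binary RR endpoint and not a mean.

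The objection also exposes a related gap. Once the sign is corrected, exactly 25% is attainable (8 → 6, 12 → 9, 16 → 12, 20 → 15), and the coding sentence assigns those participants to neither class.

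**Conclusion.** The concern holds. As printed, the rule codes none of the 210 possible improvements as a success, and every pair it does code as a success is a worsening. This follows from the Pittsburgh Sleep Quality Index section and the entry threshold alone, with no distributional assumption; only the illustrative percentages depend on assumed values. It must be corrected because it defines the variable in the primary test, even though the intended meaning is clear.

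**What to change.** In the Pittsburgh Sleep Quality Index section, replace the formula with RR = (score 0 − score 1)/score 0 × 100% and leave the 25%, 50% and 75% cut values unchanged. Each category then matches its label.

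In the same edit:

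- Use one convention at exactly 25% in both the coding sentence and the comparison sentence. The comparison sentence already counts it as a success.
- Preferably derive RR by program from the two recorded PSQI totals, not by hand. This is a safeguard and not essential to the correction.
- Recruitment began in September 2018, so check whether any RR values have already been calculated, and recompute them from the PSQI totals before unblinding.

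The cost is a short protocol correction, the same change in any analysis program, and one recalculation check. No new data or change to the sample size is needed.

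### The printed reduction-rate formula for the primary outcome has its sign reversed, so improvement on the PSQI is coded as ineffective and only worsening can be coded as success.

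*Protocol article*

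**What the plan says.** The section Pittsburgh Sleep Quality Index, under Outcome measurement, gives the whole derivation of the primary outcome.

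- Scale direction: "A higher score denotes worse sleep". The global score runs from 0 to 21.
- Baseline: "the scores the participants obtained at baseline will be recorded as score 0".
- End of treatment: "the scores obtained at the end of drug intervention will be recorded as score 1".
- Formula, which the recorder is told to apply: "RR = (score 1–score 0)/score 0*100"%.
- Bands: "RR values > 75% will be regarded as a clinical cure"; 50–75% is effective, 25–50% is success, and below 25% is ineffective.
- Binary coding: "The primary outcome is defined to have a value of 0 if RR is < 25% (ineffective) and 1 if RR is > 25"%.
- Comparison: "The proportion of 1s (i.e. RR ≥ 25%) will be compared between the treatment and placebo groups".

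The Statistical analysis section tests the primary outcome with a two-sided Fisher's exact test. The Sample size section assumes success rates of 70% on JTW and 40% on placebo. No section of the article gives an absolute value, a sign convention or another formula for RR.

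**The concern.** The formula subtracts baseline from the end score, which gives a relative increase. The bands read the result as a relative reduction. Because higher scores mean worse sleep, the two conflict: a participant who improves gets a negative RR and can never reach a success band, while a participant who worsens enough does.

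This rule produces the single variable on which the efficacy conclusion rests. If it is applied as printed, the proportion compared between arms is the proportion who deteriorated by about a quarter or more, and an effective treatment would show the lower proportion. The test is two-sided, so it would still return a p-value without flagging the direction.

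**Working it through.** **Inputs.** Score direction, score 0, score 1, the formula, the bands and the coding come from the Pittsburgh Sleep Quality Index section. The minimum baseline PSQI of 7 comes from the Inclusion criteria. The scale maximum is 21.

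**Step 1: the sign.** Improvement means score 1 < score 0. Then score 1 − score 0 < 0 and, with score 0 > 0, RR < 0. Every success band needs RR of at least +25%, so no improver can be coded 1.

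**Step 2: examples.**

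| Baseline → end | RR as printed | Code | RR with sign corrected | Code |
|---|---|---|---|---|
| 14 → 7 | (7 − 14)/14 = −50% | 0 | +50% | 1 |
| 12 → 0 | (0 − 12)/12 = −100% | 0 | +100% | 1 |
| 8 → 14 | (14 − 8)/8 = +75% | 1 | −75% | 0 |
| 7 → 21 | (21 − 7)/7 = +200% | 1 (cure) | −200% | 0 |

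**Step 3: all possible improvements.** For baselines 7 to 21 the number of lower integer end scores is 7 + 8 + … + 21 = 15 × (7 + 21)/2 = 210 pairs. None reaches RR ≥ 25% as printed. For severe baselines no end score does: the largest RR at baseline 17 is (21 − 17)/17 = 23.5%, and it is smaller at 18 to 21. Those participants could not be coded 1 whatever happened to them.

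**Step 4: the 25% boundary.** This remains after the sign is corrected. The coding sentence gives 0 below 25% and 1 above 25%; the next sentence describes the 1s as 25% or more. With integer scores an exact 25% reduction needs a baseline divisible by 4, which within 7 to 21 means 8 → 6, 12 → 9, 16 → 12 and 20 → 15.

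**Step 5: the other band limits.** Exactly 75% belongs only to the effective band, because cure is strictly above 75%. Exactly 25% belongs only to the success band, because ineffective is strictly below 25%. Only exactly 50% is shared, and both of its bands are coded 1.

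**Step 6: sample size.** The plan's inflation reproduces: 49/(1 − 0.2) = 61.25, rounded up to 62 per group, 124 in total. It takes the two success rates as inputs and does not use the RR formula, so the sign does not enter.

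**Step 7: illustration on assumed inputs.** The article gives no baseline mean and no SD of change. Assume integer scores, baseline about N(13, 3) with entry at 7 or more, and mean changes set so that 70% of JTW and 40% of placebo participants truly fall by at least 25%. The printed formula then codes as success:

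| SD of change | JTW | Placebo |
|---|---|---|
| 2 | about 0.03% | about 0.4% |
| 3 | about 0.5% | about 3.7% |
| 4 | about 1.8% | about 9.3% |

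Exact 25% reductions occur in about 2% to 4.5% of participants across these scenarios.

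**The case against.** The strongest reply is that this is an evident slip in one formula. The quantity is called a reduction rate, its largest values are labelled cure, and the sample size assumes 70% against 40% success. All three make sense only if RR is baseline minus end, divided by baseline. That stands, and it settles what was meant. It does not remove the error: the formula is printed in full as an instruction to the recorder and contradicts the labels beside it.

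Three stronger readings are tempting, and the article does not support them.

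- A reader might infer that the trial will report a reversed conclusion unnoticed. Nothing shows that the formula has been programmed as printed. An analyst who used it would probably see very few responders in either arm, far below the planned 70% and 40%, and ask why.
- A reader might infer that the sample size is wrong because it concerns the same endpoint. It does not depend on the formula.
- A reader might infer that all the bands overlap at their limits, or that an exact 25% reduction is left wholly undefined. Only 50% is shared, without effect on the binary outcome. At 25%, the success band and the sentence on the proportion of 1s both point to ≥ 25%; the single > 25% is out of line.

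**Conclusion.** The point holds as an error in the definition of the primary endpoint. The reversal follows from the article's own definitions and needs no assumption: all 210 possible improvements from an eligible baseline are coded as failures, and only worsening can be coded as success. This needs correcting before the outcome is derived, because the printed rule gives the wrong answer for the primary comparison.

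The intended direction is not in doubt and the planned 124 participants stand. The inconsistency at exactly 25% is real but minor. The as-printed success rates (about 0.03% to 1.8% on JTW and 0.4% to 9.3% on placebo) depend wholly on the assumed baseline and change distributions. They illustrate the inversion and are not a forecast for this trial.

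**What to change.** 1. State the formula as RR = (score 0 − score 1)/score 0 × 100%.
2. Define success as RR ≥ 25% everywhere, including the sentence that codes the binary outcome.
3. Keep the protocol's own limit of > 75% for cure and assign exactly 50% to one band, for example: > 75%, ≥ 50% to ≤ 75%, ≥ 25% to < 50%, < 25%. The choice at 50% does not affect the primary endpoint.
4. Before unblinding, check the derivation program, and any RR values already entered by the recorder, against the two PSQI scores.

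The cost is a short wording correction and a program check. RR can be recomputed from the baseline and end scores already being collected, so no new data are needed and the sample size does not change.

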#### Secondary outcomes

##### Polysomnography

Polysomnography (PSG) will be taken twice, at both the baseline and the end of the drug intervention. On the first night, participants will adapt themselves to the laboratory environment. On the second night, participants will be placed on PSG monitoring to record the multiple physiological sleep parameters. The parameters [20, 21] will include total sleep time, sleep efficiency, sleep latency, rapid eye movement (REM) stage latency, wake after sleep onset, and the time duration of the particular sleep stages (such as N1, N2, N3). The mean changes of all the parameters from the baseline to the end of the drug intervention will be used to measure the changes in sleep quality.

PSG is considered the gold standard for scoring sleep disorders. The scoring of sleep and arousals relies on visual inspection of continuous surface electroencephalography (EEG), electromyography (EMG), and electrooculography (EOG) during PSG and then divides human sleep into five stages: wakefulness (W); REM; non-rapid eye movement (NREM); and N1, N2, and N3 [22]. The American Academy of Sleep Medicine (AASM) defined the quantitative reference standard in PSG for adult insomnia as follows [23]: sleep latency ≥ 30 min; total sleep time < 390 min; number of wake after sleep onset (WASO) ≥ 2 or time of WASO ≥ 40 min; time in N1/total sleep time > 60%; time in N2 / total sleep time > 60% or time in N3/total sleep time < 10%, or time in REM / total sleep time < 20%. A higher or lower score corresponds to more severe symptoms.

##### ^1^H-magnetic resonance spectroscopy

^1^H-magnetic resonance spectroscopy (^1^H-MRS) will also be taken at the baseline and the end of the drug intervention. ^1^H-MRS, with its unique non-invasive advantages, is able to detect and quantify the important metabolites of living brain tissue, including N-acetylaspartate (NAA), choline (Cho), creatine (Cr), gamma-aminobutyric acid (GABA), and myo-intositol (mI) [24]. In the present study, single voxel hippocampus and thalamus metabolite ratios of GABA with Cr will be measured. The altered ratios of GABA with Cr between baseline and the end of the drug intervention will be the second outcome measure.

Studies have revealed that the GABA/Cr ratio in the frontal lobe is significantly lower [25], and the average brain GABA levels are nearly 30% lower in patients with primary insomnia [26].

##### Disharmony of Heart and Kidney Scoring System

The Disharmony of Heart and Kidney Scoring System will be used at the baseline and the end of drug intervention. It is a checklist covering one indispensable and seven accompanying items. These items are the symptoms and signs of the disharmony of heart and kidney pattern according to the theory of the pattern identification system in traditional East Asia medicine. The score of the indispensable item uses a 4-point scale (0, 3, 6, and 9) depending on the severity of the insomnia (0 = none, 9 = very severe). The seven accompanying items including palpitations, dizziness, spermatorrhea or menstrual irregularity, and night sweat and use scale of 0–4 points based on their frequency. A total score of > 9 out of 30 points is thought to demonstrate disharmony of the heart and kidney [27, 28].

Although there is no accurate evidence to explain the validity and reliability of this questionnaire, no other methods are currently available to identify the disharmony of heart and kidney pattern.

##### Blood tests

Blood tests consists of the levels of adenosine (AD) and melatonin (N-acetyl-5- methoxytryptamine) in blood samples will be recorded at the baseline and the end of the drug intervention and will then be analyzed by the clinical lab.

Sleep homeostasis in adults is affected by the sleep-regulatory substances AD and melatonin [29, 30]. AD is a product of brain metabolism and is closely related to sleep parameters. A previous study [31] showed that AD levels were elevated as a consequence of sustained wakefulness. Melatonin is an endogenous hormone produced by the pineal gland and is released exclusively at night. Melatonin has been shown to synchronize the circadian rhythms, and improve the onset, duration, and quality of sleep. Takaesu et al. thought that reduced secretion of melatonin may be involved in the mechanism of insomnia [32].

In the present study, high-performance liquid chromatography (HPLC) will be developed to determine the levels of adenosine, and an enzyme-linked immunosorbent assay will be used to detect the concentration of melatonin.

